## Abstract

**Background:**

Patient-reported outcome measures (PROMs) are used by clinical quality registries to assess patients’ perspectives of care outcomes and quality of life. PROMs can be assessed through a self-administered survey or by a third party. Use of mixed mode approaches where PROMs are completed using a single or combination of administration method is emerging. The aim of this study is to identify the most cost-effective efficient approach to collecting PROMs among three modes (telephone, postal service/mail and email) in a population-based clinical quality registry monitoring survivorship after a diagnosis of prostate cancer. This is important to assist the registry in achieving representative PROMs capture using the most cost-effective technique and in developing cost projections for national scale-up.

**Methods/design:**

This study will adopt an equivalence randomised controlled design. Participants are men diagnosed with and/or treated for prostate cancer (PCa) participating in PCOR-VIC and meet the criteria for 12-month follow-up. Participants will be individually randomized to three independent groups: telephone, mail/postal, or email to complete the 26-item Expanded Prostate Cancer Index Composite (EPIC-26) survey. It is estimated each group will have 229 respondents. We will compare the proportion of completed surveys across the three groups.

The economic evaluation will be undertaken from the perspective of the data collection centre and consider all operating costs (personnel, supplies, training, operation and maintenance). Cost data will be captured using an Activity Based Costs method. To estimate the most cost-effective approach, we will calculate incremental cost-effectiveness ratios. A cost projection model will be developed based on most cost-effective approach for nationwide scale-up of the PROMs tool for follow-up of PCa patients in Australia.

**Discussion:**

This study will identify the most cost-effective approach for collecting PROMs from men with PCa, and enable estimation of costs for national implementation of the PCa PROMs survey. The findings will be of interest to other registries embarking on PROMs data collection.

**Trial registration:**

ACTRN12615001369516 (Registered on December 16, 2015)

## Background

Patient reported outcome measures (PROMs) are designed to measure patients’ views of their symptoms, own functional status, treatment satisfaction and health related quality of life in relation to specific disease or conditions [1–4]. PROMs are an important measure of patients’ perspective of care outcomes as they provide insight into the impact of a disease and its treatment on daily lives. PROMs can assist clinicians to work with patients to achieve a level of care that meets their needs; this has been demonstrated to improve patient-provider communication [5].

PROMs may be self-administered or administered by another person (third-party). Instruments used to collect PROMs should be validated for the mode with which they are being administered. Self-administration may include surveys that patients complete on paper or electronically (e.g. via links provided in an email address to an online form or through Applications (apps) that patients can download. Tools administered by another person may include those completed on paper or electronically with assistance or those administered over the telephone [6, 7]. With the increasing number of Internet users, greater opportunities exist for collecting data, through mechanisms such as email and web-based surveys [8, 9]. An emerging trend in health-related survey research is the use of a mixed-mode approach. In the mixed-mode method, individuals may respond using a single or combination of different modes, such as only telephone or mail followed by telephone [10]. Using a mixed-mode approach compensates for the weaknesses of each individual mode at affordable cost [11]. Survey mode, length and content of the survey and incentives will impact the response rates and the cost of data collection [12].

The amount of clinical data being collected is growing exponentially; largely due to computer-based information systems [13]. In Australia, the number of known registries collecting clinical data has risen from 28 in 2006-07 to 37 in 2012 [14]. Clinical quality registries have received increasing attention as a means of improving quality and reducing the cost of health and medical care, through identifying variations in clinical practice and care, and assessing the uptake of effective treatment [15, 16]. A number of clinical quality registries collect PROMs and provide reports on outcomes to hospitals. Examples can be found in trauma [17], joint replacement [18] and renal disease [19]. PROMs are being developed by the American Society of Clinical Oncology to benchmark hospitals in relation to symptoms and functional status following cancer treatment [20].

For any individual research study, the mode of data collection is influenced by time, available resources and the population being targeted [21]. A number of studies have compared response rates using different modes of data collection [22]. A meta-analysis published in 2009 found that email surveys have lower response rates compared with mail surveys (20% vs 53% respectively) suggesting that, despite rapid growth of information technology, mail surveys appear to be superior to email in collecting survey data [22]. High response rates have been obtained when follow up attempts are intense and personalised. For example Steineck et all reported very high response rates of 89 to 99% across multiple time periods by following a regimen which included an introduction letter and a telephone call to establish contact prior to a survey being posted and a “thank you and reminder” card following return of the survey [23, 24]. It is unclear whether such a labour-intensive approach is sustainable at a population level.

Response rates have been found to vary among study populations. Postal surveys with three reminders have shown demonstrably better response rates among general practitioners compared with a telephone survey [25]. A randomised control trial (RCT) of junior medical staff and faculty members comparing electronic and postal surveys found that response rates were similar, but the average response time for electronic surveys was shorter for the residents’ group compared with the faculty group (3.8 days vs 8.4 days, p < 0.001) [26].

A recent meta-analysis by Rutherford et al. [27] investigated whether the mode of PROMs administration introduced bias into the patient reported outcome results. Findings suggested that there was no bias associated with whether PROMs were collected electronically (computer including web, touch screen, hand-held device, video conference, computer assisted telephone interview), via paper self-completion (hard copy) or via assisted completion in clinics or home. The authors of the study recommended further research using experimental designs to measure the mediators of mode effects on data quality, measurement equivalence, reliability of assessment for individuals and the impact of setting and combination of data collection method over time [27].

A cost-effectiveness study by Sinclair et al. (2012) found that postal survey costs were lower compared to both internet and telephone. The cost of a completed response using a personalised postal survey (24.75 Australian Dollars) was slightly higher than the generic postal survey, a generic internet survey and a personalised internet survey cost was almost double of a personalised postal survey and a telephone survey cost was highest among all methods [28]. Another study conducted by the Australian national stroke registry, found that telephone follow up for patient with acute stroke or transient ischemic attack was more expensive but more effective in terms of completion rates than follow-up by postal mail [16].

The Victorian Prostate Cancer Registry (PCOR-VIC) was established in 2009 to monitor treatment and outcomes of men diagnosed with prostate cancer in Victoria. PROMs are collected to assess the impact of prostate cancer diagnosis/treatment on urinary, bowel, hormonal, and sexual function and bother using the EPIC-26 survey [29]. The EPIC-26 survey has been validated for telephone and self-administered survey (paper or online) and is currently only administered by telephone [30]. The response rate has varied over time as modifications have been made to the registry and is currently at 85%. Alternative methods of PROMs administration have not been systematically assessed for their cost-effectiveness and feasibility. Although previous studies demonstrated lower response rates and in some cases increased costs of surveys delivered electronically, these were conducted several years ago and on a different population. As the PCOR-VIC is now contributing to a newly developed Prostate Cancer Registry-Australia and New Zealand, [31] the aim of this project was to assess the most cost-effective approach for collecting PROMs in a prostate cancer population.

The current study protocol describes the design of an equivalence RCT to assess the cost-effectiveness of three different methods of PROMs data collection using the EPIC-26 survey for patients diagnosed with prostate cancer.

**The primary objective** of the trial is to compare the completeness of survey data obtained using the three different data collection approaches for reporting on PROMs.

**The secondary objectives** are to:Estimate recurrent costs of data collection using telephone, postal services/mail and electronic mail (email) for PROMs data in PCOR-VIC.Compare the cost-effectiveness of the three different methods of data collection.Develop a cost projection model to estimate the cost for nation-wide scale-up of administering the PROMs data collection tool in the most efficient setting for follow up of prostate cancer patients in Australia.

## Methods/design

### Setting

Men who are diagnosed with prostate cancer in Victoria, contributing to the PCOR-VIC and who are interviewed by researchers to collect PROMS, will be invited to participate in this study. Since its establishment in 2009 the registry has expanded to 33 hospitals across the state, representing approximately 75% of the Victorian population [32]. Men are eligible for inclusion on the register if they have had a histologically confirmed diagnosis of prostate cancer that is notified to the Victorian Cancer Registry by the hospital.

### Trial design

The study design proposed for this evaluation is an equivalence RCT design. Participants will be individually randomized to one of three independent groups receiving the PROMs instrument by email, post or by telephone. Due to the nature of the intervention, it is not possible to blind the researchers or study participants.

To collect costing data we will use an Activity Based Costing (ABC) method [33] and structured questionnaires to estimate the cost of the operational activities of the three different methods of follow up. The ABC method is useful for understanding key activities of any programs and interventions and allows identification of (i) implementation levels and composition of costs; (ii) variations in how an intervention is implemented over time and associated cost implications; and (iii) resulting costs of increasing coverage of cost-effective data collection methods. This method is flexible, so its resulting estimates can be easily understood and adapted to measure the cost of data collection of the three different methods. Costs that will be considered include personnel cost, cost of supplies (e.g., envelopes, printing etc.), cost of training of data collectors and cost of operation and maintenance (e.g., telephone bill, internet bill, rent etc.) for each of the data collection methods.

### Recruitment of patients

Recruitment of patients to the PCOR-VIC has been previously described [34]. In summary, patients diagnosed in recruiting hospitals and notified by the hospital to the registry are sent details of the registry in an explanatory statement by mail. In the explanatory statement details on what data will be collected from the patient’s medical record and directly from the patient and how a man can opt off the registry if he chooses not to participate are included. The explanatory statement also contains the contact details of both the hospital where the patient was diagnosed and the university conducting the research and hosting the registry. Clinical data are collected on men who do not opt out. A waiver of consent enables clinical details to be collected from men who have died after diagnosis.

Eligible men are contacted by centrally-located university call-centre follow up staff to confirm that clinical data are accurate and up-to-date. For data collection contact is made any time within a window period of 21 days on either side of the anniversary date for data collection (henceforth recorded as the “Anniversary Date”). This is 12 months from the date of the positive biopsy for patients who do not proceed to active treatment or only receive androgen deprivation therapy; or 12 months from the date on which final initial treatment, or course of treatment finished. This is also the date for surgery and low-dose rate (seed) brachytherapy procedure. For radiotherapy and chemotherapy this is the date that the last dose of therapy was provided as well.

### Inclusion criteria

Men will be included in this study if they are eligible and have been included on the PCOR-VIC, are aged >18 years and answer the telephone when contacted by data collectors in the 21 days leading up to and including their Anniversary Date.

### Exclusion criteria

Men will be ineligible for inclusion in the RCT if they opt off the registry, have died in the period between being recruited to the registry and telephoned, do not speak English, are identified as being hearing or mentally impaired when contacted by data collectors to administer the PROMs, have been diagnosed by Transurethral Resection of the Prostate (TURP) and their treating doctor has requested that we do not contact them for follow up, or if they answer the telephone after their Anniversary Date.

## Outcome of interest

### Primary outcome

The primary outcome of interest will be effective successful follow up. Effective successful follow up is defined as providing a response to each of the 26 questions in the survey. Provision exists for patients to record “decline to answer’ on the electronic form and they are advised at the beginning of the phone call that they may chose not to answer if they wish. Responses will still be considered completed if the patient declines to answer.

### Secondary outcomes

Secondary outcome measures include time to complete an effective follow-up, and the number of occasions where answering a question was declined for each mode of survey administration.

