## Data collection, quality and monitoring methods

We will employ quantitative methods of data collection through structured questionnaires. For costing, the ABC [33] method will be adopted. Table 2 describes the data collection methods that will be used to obtain data for each specific objectives. Data will be collected by trained data collectors and supervised by the project manager and study investigators. Data collectors are from an academic institution (Monash University) and are independent of the hospitals. To ensure data quality, validation tools will be built in the web-based system. Routine monitoring meeting will also be held to ensure any problems encountered during data collection and randomization process.

**Table 2 Tab2:** Description of the specific objectives and methods

	Objectives	Methods
1	To compare the completeness of data across the three data collection approaches.	Total number of completed surveys will be identified in and compared across each of the three PROMS data collection approaches. Both the paper and electronic version provide capacity for patients to decline to answer any question. Provision in the electronic survey exists to alert patients where fields are left blank to prevent missing data issues.
2	To measure the cost of data collection of three different methods: Telephone, Mail (Postal services) and Email for Patient Reported Outcome Measures (PROMs) data in PROC-Vic.	The Activity Based Costing (ABC) method will be followed to estimate the cost of the operational activities of the three different methods of follow up. The costing data will be collected from provider perspective. Table 3: Describes the itemized costs of the 3 different methods.
3	To compare the cost and effectiveness of three different methods of data collection	Cost-effectiveness: Total cost (Personnel, recurrent, supply---)/Number of completed follow-up patients

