## Data analysis plan

### Primary and secondary outcomes

For the primary outcome measure (completeness of surveys), we will estimate individual proportions with 95% CI for each arm of the trial. We will then calculate the pooled sample proportions for each pair and the standard error of the difference. Using these measures, we will calculate the Z score test statistics. The p value will be reported for the difference and P < 0.05 will be considered as statistically significant.

For the secondary outcome measures, we will carry out independent sample t-tests to detect the difference.

Analysis will be conducted by intention to treat (ITT) [39] as well as per protocol method [40]. The ITT method will allow us to evaluate the effect of each intervention in a real life situation (i.e. when subjects are randomized to the ‘email group’ but end up in the ‘telephone’ or ‘mail’ methods instead). The per-protocol method will allow us to study the direct effect of each option.

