## Discussion

Through this economic analysis we will determine the most cost-effective means of capturing PROMs and completing follow up of prostate cancer patients through the PCOR-VIC using the EPIC-26 survey. Our primary aim therefore is to identify the value of different PROMS collection methods. Value is defined as outcomes relative to costs and encompasses efficiency [43]. The outcome we will be evaluating is response rates and representativeness of the various tools in assessing the quality of life. With knowledge of the cost of each completed survey, we will decide which approach to use as we expand data collection to obtain national coverage. Our primary objective is to assess the response rate across each data collection approach. Surveys will only be considered as completed if all relevant questions have been answered.

This will provide guidance to other registries undertaking follow up surveys of patients and it will also allow us to estimate the cost for collecting PROMs data within the Prostate Cancer Outcome Registry- Australia. Moreover we will be able to understand the quality of PROMs data collected by the three different methods. It may be that one method produces significantly higher rate of missing data or questions which patients decline to answer. We have to weigh the cost of data collection against completeness of surveys to determine the method which provides the greatest value at the end of the study. This decision will be made by the project steering committee and the funder.

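### The item-level secondary outcome counts only recorded declines, so items left blank on paper drop out of the between-mode test and can flatter mail on that outcome

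*Protocol article*

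**What the plan says.** All references are to the protocol article.

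- **Secondary outcomes:** besides time to complete follow-up, the only item-level measure named is "the number of occasions where answering a question was declined for each mode of survey administration". Blank items are not mentioned.
- **Data analysis plan, Primary and secondary outcomes:** "For the secondary outcome measures, we will carry out independent sample t-tests to detect the difference".
- **Discussion:** the comparison between methods is described more widely: "It may be that one method produces significantly higher rate of missing data or questions which patients decline to answer".
- **Table 2, objective 1:** "Both the paper and electronic version provide capacity for patients to decline to answer any question". The next sentence gives a safeguard to one form only: "Provision in the electronic survey exists to alert patients where fields are left blank to prevent missing data issues".
- **Primary outcome:** "Effective successful follow up is defined as providing a response to each of the 26 questions in the survey", with the rider "Responses will still be considered completed if the patient declines to answer". The Discussion restates the completion rule as "Surveys will only be considered as completed if all relevant questions have been answered".
- **Estimating cost effectiveness:** the effect measure in the incremental ratio is completed surveys, not the decline count.

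**The concern.** The outcome that is tested (declines) is narrower than the data-quality question the Discussion asks (missing or declined), and the part left out is not shared evenly between modes. By telephone every item is put to the man, so an unwillingness to answer is heard and can be recorded. Online, a blank triggers an alert, after which he may answer or may decline. On paper he can tick the decline option or simply move on. If he moves on, nothing is added to the count.

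A t-test between modes on this count therefore compares recording mechanisms as well as willingness to answer. It could show significantly fewer declines by mail when men are equally reluctant in every mode, and be read as evidence that mail gives better item-level data when it gives the same or less.

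**Working it through.** **The plan's own figures.** The protocol states no figure for this outcome. Its sample size belongs to the primary outcome and reproduces: 2 × 0.9 × 0.1 × (1.960 + 1.282)² / 0.10² = 189.2, rounded up to 190; 190 / 0.83 = 228.9, rounded up to 229; 3 × 229 = 687. The present point does not affect it.

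**Inputs.** The 26 items come from the protocol. The protocol does not give the rest, so they are assumptions:
- q: the chance that a man does not want to answer an item, the same in every mode
- s: the share of such items left blank on paper (the rest are marked as declined)
- a: the share of alerted online blanks that are then answered
- r: the share of mail-arm surveys finished by telephone under the fallback in Intervention B

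**Expected recorded declines per survey.**
- Telephone: 26q
- Email: 26q(1 − sa), if the same share s is first left blank and then alerted
- Mail: 26q(1 − s)
- Telephone minus mail: 26qs, or 26qs(1 − r) with telephone rescue
- Email minus mail: 26qs(1 − a)
- Declined plus blank: 26q by telephone and by mail alike

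At q = 1%, 26q = 0.26:

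| Paper non-answers left blank | Declines, telephone | Declines, mail | Mail, declined + blank |
|---|---|---|---|
| 0% | 0.260 | 0.260 | 0.260 |
| 25% | 0.260 | 0.195 | 0.260 |
| 50% | 0.260 | 0.130 | 0.260 |
| 75% | 0.260 | 0.065 | 0.260 |
| 100% | 0.260 | 0.000 | 0.260 |

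For email, the alert matters. With s = 100% and a = 80%, email records 0.26 × 0.2 = 0.052 against 0 by mail. With a = 100% the gap is nil.

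**False-significance rate.** This was simulated with 3,000 trials per setting, 206 surveys per arm (0.9 × 229), beta-binomial non-answers over 26 items (shape 0.3), equal willingness in both modes, and a two-sample test at 5% on the count per man.

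| Setting | q = 1% | q = 2% | q = 4% |
|---|---|---|---|
| Half of paper non-answers blank | 67% | 83% | 93% |
| A quarter blank | 18% | 25% | 32% |
| Half blank, 30% of mail arm finished by telephone | 33% | 46% | 58% |
| None blank | 5% | 5% | 5% |

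Repeat runs of the first row at 1% gave 65% to 67%. Other settings at 1%:
- a tenth of paper non-answers blank: about 7%
- email against mail, half blank: about 28% if half of alerted items are answered, 8% if 80% are, and about 5% if all are
- email against mail with half of alerts answered and 30% telephone rescue: about 8%
- much more skewed non-answering (shape 0.05), half blank: below 30%

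**The same blanks on the primary outcome.** A paper survey is complete only if no item is blank. Treating items as independent, that probability is (1 − qs)^26. At q = 1% and s = 50% it is 0.995^26 = 87.8%, against 100% if every online non-answer ends as an answer or a decline. Clustering of blanks within men would make the paper figure higher. The direction is opposite to that on the decline count.

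**The case against.** The strongest reply has five parts.

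1. **Paper has a decline option.** Table 2 says so. A reader might infer that reluctance scores one by telephone or email and always nothing by mail. That does not follow: a man who uses the option is counted. The bias needs some items to be left blank.
2. **The alert need not produce declines.** A reader might infer that online blanks become declines. Table 2 says only that the patient is alerted, and he may answer. The email–mail gap therefore shrinks and can vanish. The telephone–mail comparison does not depend on the alert.
3. **Blanks are not ignored.** A reader might infer that mail would look best overall. The documents do not support this: a blank fails the primary definition and lowers the completed surveys in the cost-effectiveness ratio. This stands, and it confines the bias to the secondary outcome. It does not repair that outcome, because the primary result is yes or no per man and cannot show how many items are missing.
4. **The decision rests elsewhere.** The Discussion's explicit trade-off is cost against completeness, so the decline count alone would not settle the choice of method. That stands, although the Discussion does name missing and declined items as part of what it expects to learn. The list of secondary outcomes is also not worded as exhaustive, but no outcome counting missing items is named.
5. **The high simulated rates come from a favourable corner.** They use half of paper non-answers blank, no telephone rescue, and 206 per arm although the protocol already calls the 229 respondents. Men with a blank are not completers under the primary definition, so the 206 can only mean surveys returned or answered. Analysis by randomised arm mixes modes and dilutes the gap. This stands, and it is why only a range is reported.

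**Conclusion.** The point holds as a mismatch in the definition of a secondary outcome. What is counted and tested is narrower than the comparison the Discussion describes, and the omitted part (blank items) can arise freely on paper but is prompted online and voiced by telephone. Mail can therefore look better than telephone on the decline count whenever some paper items are left blank, even with equal willingness to answer. Against email this is only a possibility, depending on what men do after the alert.

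The size cannot be fixed from the document. At an assumed 1% item non-answer rate, the false-significance rate lies between about 5% and about 67%, depending on the share of paper items left blank, the response to alerts and the amount of telephone rescue. The primary comparison, the sample size and the cost-effectiveness ratio are not biased in mail's favour by this. There the same blank counts against mail, so the primary and secondary results can give opposite signals from one behaviour. This is a moderate issue that should be corrected.

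**What to change.** - In Secondary outcomes, define the item-level measure as the number of the 26 items without a substantive answer, whether declined or blank, per returned or answered survey, identically for telephone, mail and email.
- In the data analysis plan, use that total for the between-mode test.
- Report declined and blank counts separately by mode as descriptive results.

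The cost is a change of wording. The primary outcome already requires each of the 26 items to be checked for a response, so blanks have to be identified anyway. The protocol does not say whether data entry from paper separates a blank from a decline. If it does not, the descriptive split needs one extra entry code. The sample size and the primary analysis do not change.
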